### Outcomes and their assessment

The main primary and secondary outcomes will be assessed using anonymised routine electronic health records data that are already captured at participating organisations. These data will be extracted from NHS databases and anonymised by local organisation informatics/information technology departments (funding is provided to support this) before sending to the research team, following a pre-defined data specification document detailing data items and coding. All patients can request that their NHS records not be released for secondary use (for example, in Hospital Episode Statistics (HES)). Patients who have opted out of sending their hospital records to NHS Digital will not have information submitted for intervention evaluation.

The phase III main trial has two co-primary outcomes:30-day mortality post-admission (non-inferiority)DDDs of antibiotics per acute/general medical admission (superiority).

Admission (rather than bed-day) is the denominator for this co-primary outcome (similar to the DH Antimicrobial Prescribing Quality Measures), because bed-day can be strongly influenced by non-medical reasons for not discharging inpatients [46, 47]. The reason for including two co-primary outcomes is to include both a patient health outcome, where we expect to see no evidence of benefit from using fewer antibiotics, but importantly no evidence of harm; and also an endpoint reflecting the overarching goal of the intervention, namely to reduce antibiotic use. However, the full trial will not evaluate a shorter course of antibiotics per se, but an intervention designed to reduce antibiotic duration enacted through healthcare professionals’ behaviour. There is therefore no guarantee that it will have the desired effect on total antibiotic usage: if the intervention does not reduce antibiotic consumption, de facto it will have failed. For this reason, antibiotic consumption is a co-primary superiority endpoint. The fact that the primary endpoint (30-day mortality) is for non-inferiority is another reason for including antibiotic duration as a co-primary endpoint; the intervention will be considered successful only if it significantly reduces antibiotic usage with no evidence of increased mortality.

No personal data are collected, but as date of death is considered confidential (but not personal as it does not relate to a living individual), approval has been obtained from the Research Ethics Committee (REC) and the Confidentiality Advisory Group (CAG) for data collection without individual consent.

The primary and secondary outcomes (Table 1) will be supplemented by additional quantitative, qualitative and laboratory data in order to assess uptake, use and other impacts of the intervention (also listed in Table 1). Gut flora resistance potential will be assessed using repeated point prevalence surveys at three organisations, following the stepped-wedge randomised design using freshly discarded faecal samples remaining after *Clostridium difficile* testing. Diarrhoea is very common in acute/general medical inpatients, with multiple causes, the majority not infectious. All inpatients with diarrhoea will have samples sent for *C. difficile* testing, making this a relatively generalisable reflection of the population, particularly of those patients likely to provide the greatest contribution to spreading resistance elements by the oral-faecal route (because they have diarrhoea) and who have received antibiotics (because antibiotics can cause diarrhoea). Less than 5% test positive for *C. difficile*; that is, the actual disease burden is low. Samples will be identified for the study by staff in the routine service microbiology laboratory. They will be analysed for gut flora ‘resistance potential’ without respect to any patient-identifying information, and ethical approval has been obtained to do this without individual patient consent. No single method is currently available to estimate the ‘resistance potential’ of gut microorganisms. Culture is specific to particular organisms and is practically feasible for only a small number of species, excluding any that are non-culturable by default. Targeted molecular approaches, such as polymerase chain reaction (PCR), can only identify a subset of thousands of known variants of antimicrobial resistance (AMR) genes/mutations in a sample [48]. Because of this, we plan to use metagenomic sequencing directly from extracted faecal DNA to characterise the gut ‘resistance potential’, comparing the millions of short sequences produced to catalogues of thousands of AMR genes, and theoretically providing a quantitative and representative estimate of ‘resistance potential’ [49, 50].

**Table 1 Tab1:** Primary, secondary and other objectives and measures in the main trial

Objectives	Outcome measures	Timepoint(s) of evaluation of this outcome measure
Co-primary objectives		
To compare the effect of introducing the behavioural intervention on 30-day mortality post-admission as an acute/general medical inpatient (non-inferiority)	Death, ascertained from hospital records which are routinely updated from national death reporting	30 calendar days after admission to acute/general medicine
To compare the effect of introducing the behavioural intervention on antibiotic exposure per acute/general medical admission (superiority)	Defined daily doses (DDDs) of antibiotics per acute/general medical admission, ascertained from electronic hospital prescribing records	Over each acute/general medical admission, including antibiotics prescribed at discharge
Secondary objectives		
To compare the effect of introducing the behavioural intervention on antibiotic exposure using different metrics	DDD per occupied bed-day, days on antibiotics per admission and bed-day (length of therapy (LOT)),^a^ antibiotic days per admission and bed-day (days of therapy, DOT^a^), carbapenem DDD, DOT^a^ and LOT^a^ (per admission and per bed-day), broad-spectrum DDD, DOT^a^ and LOT^a^ (per admission and per bed-day), IV and oral DDD, DOT^a^ and LOT^a^ (per admission and per bed-day), WHO-defined ’Access’, ’Watch’ and ’Reserve’ DDD, DOT^a^ and LOT^a^ (per admission and per bed-day), ’Access’ as a percentage of all antibiotic use	Over each acute/general medical admission, including antibiotics prescribed at discharge
To compare the effect of introducing the behavioural intervention on adverse outcomes	ICU admission during the current admission, total length of stay (hours), antibiotic restart after discontinuation,^a^ emergency re-admission in the 30 days after discharge, *C. difficile* diarrhoea, mortality over the longer term	ICU admission over the current admission; for emergency re-admission, up to 30 days post-discharge; for *C. difficile* diarrhoea, up to 90 days post-admission; for mortality up to 90 days post-admission
To evaluate the impact of the intervention on the faecal flora	Proportion of discarded faecal samples from medical inpatients from which extended spectrum beta-lactamase (ESBL)-carrying *Enterobacteriaceae* can be isolated	Repeated cross-sectional surveys over time
Tertiary objectives		
To evaluate the cost-effectiveness of the behavioural intervention	Resource utilisation and costs	Over the current admission and up to 30 days post-discharge
To quantify uptake and acceptability of the online training component of the behavioural intervention (process outcome)	Proportion of locally identified and pre-specified essential individuals who drive prescribing decisions for acute/general medical inpatients at the organisation who complete the online training (recorded electronically by individuals entering their name and work (NHS) email on the last page) or on an attendance list if the local organisation has opted to do face-to-face training sessions	Within 3 months of invitation to complete training
To quantify uptake of the ARK ‘review and revise’ procedure within the behavioural intervention (process outcome)	Proportion of regularly audited antibiotics prescriptions which document the ARK classification criteria Proportion of regularly audited antibiotics prescriptions which are stopped at ‘review and revise’	Over 12 weeks following implementation date

^a^In organisations with individual electronic prescribing (rather than bulk) antibiotic data

Note: WHO definitions of ’Access’, ’Watch’ and ’Reserve’ antibiotics will be used, following the 2017 Essential Medicines List, using the PHE interpretation. Broad-spectrum is defined as co-amoxiclav; piperacillin/tazobactam; second (e.g. cefuroxime), third (e.g. ceftriaxone ceftazidime) or fourth (e.g. cefepime) generation cephalosporins or cephalosporin-beta-lactamase inhibitor combinations (e.g. ceftazidime-avibactam, ceftolozane-tazobactam); carbapenems; quinolones; azithromycin; tigecycline; aztreonam; and telithromycin. Cefaclor is not included as a second generation cephalosporin because it is administered orally and is not well absorbed

Process evaluation will also include interviews/focus groups with healthcare professionals, a brief questionnaire concerning healthcare professionals’ perceived barriers to review and revise (collected online on completion of the online training and 1 month later) and healthcare professionals’ usage of the online training (collected automatically by the website and mobile software). Implementation of ARK will also be assessed using a questionnaire completed by the ARK champion.

There is intense interest in the use of electronic health records in clinical trials [51]. However, they also have important challenges, three being notable for the ARK intervention: defining the intervention population; assessment of antibiotics; and access.

Firstly, the population receiving the intervention is (adult) acute/general medical inpatients. However, in practice different organisations have different patient pathways; some organisations retain patients in acute medical units for the duration of their admission, whereas in others they swiftly move to related specialties such as gastroenterology, gerontology, respiratory, etc. Part of the implementation toolkit involves mapping these patient flows and involving all relevant clinicians in training. However, such acute/general medical inpatients are not always identified by the use of the 300 (general medicine) specialty code (Fig. 1). In 2017 the Society for Acute Medicine and the Nuffield Trust ([name], personal communication) completed an exercise identifying the most commonly used specialty codes under which adult acute/general medical inpatients are admitted, and we follow their definition. The patient population is therefore defined by either the treatment specialty code (under which the patient is treated) (HES “tretspef”) or the main specialty code (of the consultant) (HES “mainspef”) of either the first or second consultant episode for an inpatient spell, where the inpatient spell has the primary admission date (HES “admidate”) during the time periods specified previously. Paediatric admissions have different specialty codes and are not included in this definition of the analysis population (and are not exposed to the intervention, which is implemented in services admitting adult acute/general medical inpatients).

Because of the potential for exposure misclassification (which may vary by organisation), sensitivity analyses of the primary outcomes will be conducted excluding cardiology (320), rheumatology (410), haematology (303) and neurology (400). If results provide a qualitatively different interpretation, these sensitivity analyses will be conducted for all outcomes.

DDDs using standard WHO formulae (www.whocc.no) are designed to transform milligrams of different antibiotics into standard units reflecting a typical dose and are recommended for use in antibiotic evaluations [52]. Their most important limitation is that reducing prescribing of broad-spectrum antibiotics often involves moving to a combination of multiple agents of narrower spectrum. A single DDD of a broad-spectrum antibiotic may therefore be replaced with multiple DDDs of narrower spectrum antibiotics, but this is probably better for future antimicrobial resistance. For this reason, where organisations are able to provide individual-level antibiotic prescribing data, we will also analyse length of therapy (LOT), defined as the time (days/hours/minutes) between the last and first administration of antibiotic treatment (lumping all antibiotics together), and days of therapy (DOT), defined as the sum of the time (days/hours/minutes) between the last and first administration of each separate antibiotic. However, relatively few organisations currently have individual-level electronic prescribing systems, and therefore most are only able to provide bulk-level DDDs in acute/general medical inpatients.

Admission (rather than bed-day) is the denominator for antibiotic usage (similar to the UK DH Antimicrobial Prescribing Quality Measures), because bed-day can be strongly influenced by non-medical reasons for not discharging inpatients. However, this provides a challenge since it is not straightforward to identify these admissions from the electronic inpatient admission records (see the preceding discussion). Where hospitals provide data on bulk prescriptions only (e.g. using the JAC or Rx-info systems), they are able to provide both total DDDs and DDDs per admission to the relevant hospital areas. The primary analysis will use this denominator wherever available. Where these data are not available, we will use estimates of the relevant admissions and overnight stays from the population defined above.

The last challenge is obtaining the data from individual organisations. Most do not have single unified systems, so patient admissions, antibiotic usage (bulk DDDs or individual level prescriptions) and *C. difficile* data are all held on separate databases and have to be extracted, merged and pseudo-anonymised by overworked information technology departments. This is proving to be a significant challenge despite £14,000 per organisation being provided to obtain these data four times over the course of the trial (for Data Monitoring Committee [DMC] meetings and final analysis).

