The primary analysis method for binary outcomes will be logistic regression. This is done because, for mortality, data will be considered to be completely ascertained on the basis of routine checks that each organisation conducts against the national death registry, for example, to ensure that follow-up letters are not sent to patients who have died. Therefore, patients not recorded as dying in the national system will be assumed to be alive 30 days (co-primary outcome) and 90 days (secondary outcome) after admission. The death registry is not up to date in real time, and routine checks are only carried out periodically; the final data extract will be requested 6 months after the last included admission to ensure that ascertainment is as robust as possible. In-hospital mortality is completely ascertained by discharge codes. Further, for all binary outcomes, event rates are relatively low (5–10%), so there is little difference between analysing a cause-specific hazard or a competing risks subhazard. Analysing the outcome using logistic regression also facilitates visualisation of the estimated pre- and post-implementation trends, and the step change at implementation, against the observed percentages for each outcome per organisation. Sensitivity analyses will consider these as time-to-event outcomes and will consider competing risks from inpatient and out-of-hospital deaths as relevant for each specific outcome [53–55]. Negative binomial regression will be used to model antibiotic DDDs, incorporating over-dispersion and using different offsets as defined previously. Other antibiotic outcomes are planned to be analysed using ordinal logistic regression; however, if, for example, data are approximately normally distributed, either before or after transformation, linear regression may be used instead. Box-Cox-transformed length of stay will be analysed using normal linear regression. A sensitivity analysis will include stay only up to the point a patient was declared medically fit for discharge. A second sensitivity analysis will use quantile regression of the 90th percentile to assess effects at the extremes of the distribution.

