Each outcome will first be modelled separately in each organisation, estimating trends before and after intervention implementation, plus an implementation-associated immediate effect (‘step change’) (Fig. 2). The unit of analysis will be admission. Patient will be used as a clustering variable for robust variance adjustment (but not otherwise adjusted for). Based on data available to date, we do not expect strong seasonal effects in the outcomes above, but this will be investigated and included if necessary. Meta-analytic techniques will then be used to combine these organisation-specific estimates to produce an overall intervention effect, assessing heterogeneity using *I*^2^ statistics. This approach is similar to a multilevel model, but it has more flexibility in modelling individual organisations. The primary comparison will be a 2 degree of freedom test, jointly testing that the ‘step change’ is zero and that there is no change in calendar trends post- vs pre-implementation. This joint test will be fitted on model parameters and explicitly account for correlation between the two estimands. Secondary analyses will consider calendar trends post-implementation, and change in calendar trends post- vs pre-implementation, and a trend for implementation over 3 months rather than a ‘step change’.

The major concern about unadjusted analyses is the potential for variation in case mix, particularly over a calendar year, to affect estimates of intervention effect. Additional sensitivity analyses will adjust for case mix to assess whether changes in case mix could confound any changes in antibiotic use observed over time. The following admission-level covariates have been chosen based on their significant effects on 30-day mortality in previous analyses of emergency admissions from routinely collected data [57] and will be adjusted for in each organisation regardless of statistical significance (with non-linear relationships between covariates and outcomes assessed and incorporated using natural cubic splines): sex; age (years) at admission; immunosuppression; Charlson Co-Morbidity Index (defined using secondary diagnosis codes); interaction between age and Charlson [57]; patient classification; admission method, source, specialty, day of the week, time of day and day of year and interaction between admission day of the week and time of day [57]; number of admissions in previous year (excluding as day case), and ever had a complex admission.

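### The adverse ICU outcome counts ICU stays that began before the patient reached acute/general medicine, which pulls its relative effect towards 1 by an unknown amount

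*Protocol article*

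**What the plan says.** Three statements in the protocol article combine.

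- **Population** (Outcomes and their assessment). A spell qualifies on the treatment or main specialty code "of either the first or second consultant episode for an inpatient spell". It is dated as a whole: "where the inpatient spell has the primary admission date (HES “admidate”) during the time periods specified previously".
- **Outcome** (Table 1, secondary objectives). Under the objective "To compare the effect of introducing the behavioural intervention on adverse outcomes", the measure is "ICU admission during the current admission" and the evaluation window is "ICU admission over the current admission".
- **Analysis** (Statistical analysis). "The unit of analysis will be admission", and "The primary analysis method for binary outcomes will be logistic regression".

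Nothing in the article orders the ICU stay against the qualifying episode. By contrast, the 30-day mortality row of the same table starts its clock at admission to acute/general medicine.

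**The concern.** Take two spells. In spell A the patient is in ICU during a first episode with a non-qualifying code, then steps down to general medicine for the second episode. In spell B the patient is in general medicine, has antibiotics stopped at review, deteriorates and goes to ICU. Both are in the population and both score 1. Spell B is the kind of event the outcome exists to detect. In spell A the ICU stay is over before acute/general medical care starts, so it is unlikely to reflect stopping antibiotics there.

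Events like A form a background that is roughly the same before and after implementation. On the relative scale of a logistic model they move the estimate towards no effect. For a harm outcome, in a trial whose aim is a safe reduction in antibiotic use, that is the unfavourable direction.

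The definition also carries weight because the other direct in-hospital sign of failed stopping, antibiotic restart, is available only in organisations with individual electronic prescribing, which the article says are few. ICU admission has no such restriction.

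**Working it through.** The article gives no ICU-specific event rate, effect size or power, so there is no stated figure to reproduce. Its stated power concerns the co-primary outcomes only.

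**Inputs**

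- f: the share of pre-implementation ICU events that began before the first qualifying episode. Not in the documents; 0.1, 0.3 and 0.5 are assumed for illustration.
- R: the true risk ratio for ICU admissions starting on or after that point. 1.20 is assumed.
- p: the overall pre-implementation ICU event rate. Statistical analysis puts binary outcomes in general at 5–10%; 5% is used below.
- Also assumed: a first episode in ICU does not itself carry a qualifying code (the figure defining the population is not shown), earlier stays do not change with the intervention, and few spells contain both an earlier and a later ICU stay.

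**Step 1: dilution of the risk ratio.** Before implementation the event rate is p = fp + (1 − f)p. Afterwards it is fp + (1 − f)pR. The observed ratio is f + (1 − f)R, and its excess over 1 is (1 − f)(R − 1).

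| f | calculation | observed ratio |
|---|---|---|
| 0.1 | 0.1 + 0.9 × 1.20 | 1.18 |
| 0.3 | 0.3 + 0.7 × 1.20 | 1.14 |
| 0.5 | 0.5 + 0.5 × 1.20 | 1.10 |

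**Step 2: the odds ratio, which the model estimates.** With p = 5%, a risk ratio of 1.20 is an odds ratio of (0.06/0.94)/(0.05/0.95) = 1.213. At f = 0.1 the later rate is 5.9% and the odds ratio is (0.059/0.941)/(0.05/0.95) = 1.191. At f = 0.3 it is (0.057/0.943)/(0.05/0.95) = 1.148. The shrinkage is almost the same: 0.191/0.213 = 0.90 and 0.148/0.213 = 0.69, or 0.70 before rounding.

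**Step 3: the absolute difference.** The change in rate is (1 − f)p(R − 1) under either definition. At p = 5% and f = 0.1 it is 0.9 × 0.05 × 0.20 = 0.9 percentage points. The risk difference is therefore noisier under the current definition, but not biased.

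**Step 4: does dropping the earlier stays cost power?** The absolute difference is the same under both definitions, so the required sample sizes are in the ratio of the summed binomial variances (p = 5%, R = 1.20).

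- f = 0.1: current 0.05 × 0.95 + 0.059 × 0.941 = 0.1030; post-entry only 0.045 × 0.955 + 0.054 × 0.946 = 0.0941. Ratio 1.10.
- f = 0.3: current 0.05 × 0.95 + 0.057 × 0.943 = 0.1013; post-entry only 0.035 × 0.965 + 0.042 × 0.958 = 0.0740. Ratio 1.37.

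The current definition needs about 10% or 37% more admissions for the same power. These ratios ignore clustering and the interrupted time series model, so they are only a guide to relative efficiency.

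**Step 5: do the planned safeguards reach this?** The sensitivity analysis for exposure misclassification drops four specialties, starts with the primary outcomes, and does not concern timing. Case-mix adjustment is itself a sensitivity analysis and does not address the order of events.

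**The case against.** **An ordering rule may exist elsewhere.** The article condenses a full protocol, and extraction follows a separate data specification; neither is shown, nor is the analysis plan. A rule there would settle the matter. But Table 1 does state a measure and a window for this outcome, and followed as written they count the earlier stays.

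**Earlier ICU stays are not wholly outside the intervention's reach.** A reader might infer that only ICU transfers after general medicine can be harm. The documents do not support that. The Intervention section applies the decision aid to initial prescriptions and names the emergency department among the settings and the decision makers. The Health economics section allows that initial prescribing may change. Some patients who go from the emergency department to ICU may already have been exposed. This stands, and is why the point says largely, not entirely, unattributable.

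**The coded episode start is an imperfect time zero.** The article itself warns that specialty codes do not always identify these patients and that misclassification may vary by organisation. A patient managed in acute medicine under a non-qualifying code, then sent to ICU, would lose a genuine event under a strict ordering rule. This also stands, and is a reason to report both versions.

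**Other dilution remains.** Patients never given antibiotics, and ICU transfers before review, still count under any definition, because outcomes cover all admissions. That is true of the design in general. It does not argue for keeping a component that the hospital records can separate.

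**Drift in step-down pathways.** A reader might infer that changes in critical-care step-down would be mistaken for an intervention effect. Nothing in the article suggests such changes coincide with the randomised dates, and the within-organisation model includes trends before and after implementation. That inference is not made here.

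**Conclusion.** The point holds for the definition as printed. A spell can qualify through its second episode, any ICU admission in the spell is an adverse event, and stays that began in an earlier non-qualifying episode are therefore counted. On the planned relative scale they shrink the excess risk by (1 − f): a true 1.20 reads as 1.18 if one event in ten came earlier and 1.14 if three in ten did.

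The size is unknown because f appears nowhere in the documents, and at a small f the effect is slight. The calculation also rests on the earlier stays being unaffected by the intervention, which is approximately rather than strictly true.

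A reader might infer that the trial's safety conclusion is undermined. It is not: that conclusion rests on co-primary 30-day mortality, which this does not touch. What is weakened is one secondary harm outcome.

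**What to change.** In Table 1, define the adverse ICU outcome as an ICU admission starting on or after the start of the first qualifying acute/general medicine episode. Spells that qualify through their first episode are unaffected.

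Report any ICU admission in the spell alongside it as a sensitivity analysis, since specialty coding is imperfect and exposure in the emergency department is possible. Report the share of ICU stays that came before the qualifying episode, before and after implementation, so that readers can see f.

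Do not adjust for earlier ICU as a covariate. It may follow exposure to the intervention, so adjusting for it could remove part of an effect.

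The cost is one line in the outcome definition and one extra analysis. The data specification must include ICU and episode start dates. There will be fewer ICU events, although under the assumptions above the events removed contribute noise and no intervention effect.

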However, a 2013 survey of National Health Service (NHS) antibiotic pharmacists found that although 95% of 105 responding English trusts included early antibiotic review in their policies/guidelines, only 48% conducted any compliance monitoring [29]. Where compliance was monitored, relatively few (< 20%) prescription changes of any kind were made. This agrees with studies reporting clinicians’ reluctance to modify antibiotic prescribing decisions made by others, even when a patient’s clinical status has evolved [30] and reflects the complexity of decision making on antibiotic prescribing [31]. Trust policies frequently recommended antibiotic durations of ≥ 7 days [29], suggesting lack of review could lead to substantial overuse. Even by 2017, < 10% of antibiotic prescriptions were discontinued at review [32], despite studies suggesting that 20–30% of prescriptions could be stopped safely [33]. Despite considerable variation in local guideline-recommended antibiotic duration and practice [29], there are no data showing whether or not trusts which routinely use fewer antibiotics have higher rates of adverse outcomes.

This failure of prescribers to change or stop antibiotics is perhaps unsurprising given the lack of evidence to inform how ‘review and revise’ should be implemented. Of 221 hospital antimicrobial stewardship interventions included in a Cochrane review [34], only 14 even collected duration of antibiotic therapy as an analysable outcome, let alone directly targeted it; many of these studies evaluated the introduction of procalcitonin testing as a mechanism to reduce antibiotic durations. Other interventions included introducing guidelines/policies and education/feedback. Interventions specifically designed to reduce antibiotic duration were not evaluated as a category, but overall duration of antibiotic treatment decreased by 1.95 days with stewardship interventions. One large study (*n* = 462) [35] found an intervention incorporating face-to-face pharmacist feedback significantly reduced antibiotic durations for lower respiratory tract infections in intensive care. However, another study found no impact of prescription review by telephone [36], illustrating the importance of specific intervention components.

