Process evaluation analyses will seek to better understand how ARK was implemented across different hospitals, potential barriers and facilitators and also how implementation influenced use of the intervention and antibiotic use. This will be triangulated with data from qualitative interviews/focus groups, which will undergo thematic analysis. Secondary analyses will consider how much of any effect of the intervention could be mediated through different aspects of the implementation of review and revise, including training completion rates, evidence of implementation from audit records as well as success of implementation in each hospital, based on mixed methods evaluation and documentary evidence, and number of the preceding criteria met.

For the primary endpoint, subgroup analyses will be conducted by investigating heterogeneity in the organisation-level intervention effect estimates across the following factors, using meta-regression techniques: randomisation block (categorical stratification factor), calendar period of randomised implementation date (reflecting different NHS pressures) (Jan–Mar, Apr–Jun, Jul–Sep, Oct–Dec), organisation type (small, medium, large, teaching), region, functional role of champion (acute medicine, microbiology/infectious diseases, pharmacist), paper vs electronic prescribing systems, percentage of essential people completing training by 12 weeks, total number completing training by 12 weeks per 100 acute beds.

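### Table 1 measures uptake of review and revise partly by an audited stopping rate taken only after implementation, so the level mixes existing practice with uptake

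*Protocol article*

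**What the plan says.** In Table 1 (Outcomes and their assessment), one tertiary objective is to quantify uptake of the ARK review-and-revise procedure, labelled a process outcome. It has two measures:

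- "Proportion of regularly audited antibiotics prescriptions which document the ARK classification criteria"
- "Proportion of regularly audited antibiotics prescriptions which are stopped at ‘review and revise"

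They share one timepoint: "Over 12 weeks following implementation date". No pre-implementation period and no comparison are named.

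Four other places bear on this:

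- Background gives stopping before ARK: "Even by 2017, < 10% of antibiotic prescriptions were discontinued at review". It also says that studies suggest "20–30% of prescriptions could be stopped safely".
- Intervention lists stopping rates among the data that the audit component collects.
- Statistical analysis makes submission of baseline audit data by the implementation date one of the eight fidelity criteria, with initial post-implementation audit data due by week 4.
- Statistical analysis also plans secondary analyses of how far any effect is mediated through implementation, "including training completion rates, evidence of implementation from audit records", success of implementation in each hospital, and the number of fidelity criteria met.

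**The concern.** The two measures differ in kind. Documentation of the ARK categories is specific to the intervention, so a level after implementation reads directly as uptake. Stopping at review is one of the options in national guidance that dates from 2011, and it took place before ARK. A level observed only afterwards is existing practice plus whatever changed.

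This also departs from the trial's own reasoning. The Randomisation section confines comparisons to before versus after in the same trust, because comparisons across trusts are confounded by organisational change. Reading post-only stopping rates as uptake, organisation by organisation, is a cross-trust comparison. An organisation that stopped many prescriptions before ARK and changed nothing would look like high uptake. One that rose from very little to a moderate level would look like low uptake.

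At stake is the interpretation of a process outcome and, if this proportion is carried into the mediation work, the apparent link between implementation and effect.

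**Working it through.** The article states no figure for this measure, so there is nothing to reproduce. The arithmetic below only shows how much the choice could matter.

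**1. Share of the post level already present**

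Inputs: baseline stopping of 5% or 10% (assumed; 10% is the limit of the stated figure of under 10%); post level of 20% or 30% (assumed equal to the range that Background says could be stopped safely).

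Change = post − baseline. Share already present = baseline / post.

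| Baseline | Post | Change (points) | Share already present |
|---|---|---|---|
| 5% | 20% | 15 | 5/20 = 25% |
| 5% | 30% | 25 | 5/30 = 17% |
| 10% | 20% | 10 | 10/20 = 50% |
| 10% | 30% | 20 | 10/30 = 33% |
| 10% | 10% | 0 | 10/10 = 100% |

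With a 2% baseline the share falls to 2/30 = 7% up to 2/20 = 10%. The last row of the table is the case that the post-only measure cannot detect: a non-zero rate with no uptake.

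**2. If the post level were used as an organisation-level mediator**

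Suppose the organisation's effect depends on its change in stopping, and that baseline and change are independent (assumed). The slope on the post level is then multiplied by SD_change² / (SD_change² + SD_baseline²). SDs are in percentage points and all are assumed.

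| SD change | SD baseline | Factor |
|---|---|---|
| 5 | 1 | 25/26 = 0.96 |
| 5 | 3 | 25/34 = 0.74 |
| 5 | 5 | 25/50 = 0.50 |
| 3 | 5 | 9/34 = 0.26 |

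The loss runs from negligible to large, and the article gives nothing that narrows this range.

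**3. Whether a change score is better in that model**

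This formula ignores audit sampling error. Subtracting the baseline audit removes the true baseline variance but adds the sampling variance p(1 − p)/n. With p = 10% and n = 50 audited prescriptions (assumed; no audit size is given), the sampling SD is √(0.10 × 0.90 / 50) = 4.2 points. That exceeds a true baseline SD of 3 points, so the change would be the more attenuated predictor. Break-even is n = 0.09 / 0.03² = 100 baseline prescriptions per organisation for an SD of 3 points, and 0.09 / 0.05² = 36 for an SD of 5.

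**4. Precision of the change**

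With 50 prescriptions in each audit, rates of 10% and 20%, and simple random sampling (all assumed):

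- Post level: 1.96 × √(0.20 × 0.80 / 50) = ±11.1 points.
- Change: 1.96 × √(0.0018 + 0.0032) = ±13.9 points.

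**The case against.** The strongest reply is that this row is descriptive. Table 1 words its effect rows as comparisons of the intervention's effect, whereas this one only quantifies uptake, and it includes an ARK-specific measure beside the stopping rate. Baseline audits are planned and nothing says that they will go unreported. The co-primary rows do not state comparators in the timepoint column either, and such detail may sit in the SAP or full protocol.

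Much of this stands, and it limits the point. It does not remove it. The co-primary timepoints are windows for each admission, applied both before and after implementation. The timepoint here is a calendar window that starts at implementation and so excludes the baseline audit. That is a stated choice, not an omitted detail.

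A reader might infer two stronger things that the documents do not support.

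- That prior stopping is credited to ARK as an effect. It is not: ARK's effect on antibiotic use and mortality is estimated from before-and-after models within each organisation.
- That the mediation analysis uses the wrong mediator. The Statistical analysis section names audit evidence only in general terms, among several candidates. It fixes no window and does not name the stopping proportion; category documentation would fit the description equally well. The pre-specified meta-regression uses training measures, not stopping.

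**Conclusion.** The point holds for the stopping proportion in Table 1. Evaluated only after implementation, it is a level that mixes existing practice with uptake, while the measure beside it does not have this problem. Any consequence for mediation is conditional on that proportion being carried over as defined.

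The size cannot be established from the article, which gives no post-implementation stopping rate, no between-organisation SD of stopping and no audit size. Background reports variation in recommended durations and practice, and the Design section expects prescribing to vary more between organisations than within them; neither is a figure for stopping at review. The shares and attenuation factors above are illustrations only.

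This is a minor improvement to a tertiary process outcome. Sample size, the co-primary analyses and the secondary outcomes are untouched.

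**What to change.** - In Table 1, for the stopping proportion only, set the timepoint to the baseline audit plus the 12 weeks after implementation. Report the baseline rate, the post level and the within-organisation change with a confidence interval. Leave documentation of the ARK categories post-only.
- In the Statistical analysis section, say which audit measure enters the mediation analysis. If it is the stopping proportion, account for the baseline level, for example by including baseline and post rates together and allowing for audit sample size. Neither the post level alone nor a bare change score is safe by default.
- Describe the change as before versus after. It would not remove other influences over the same period, such as the financial incentives that the article mentions.

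Cost: wording only, provided that the baseline audit records stopping; the article lists stopping rates among the audit data but does not itemise the baseline audit. The interval for the change is wider than for the post level, and organisations without a baseline audit drop out of this one measure.
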